### Recruitment

Consecutive patients admitted to the adult ICU will be screened daily for eligibility by the principal investigator. Eligible patients or their legally authorised representatives will receive verbal and written information about the study. Written informed consent will be obtained before any study-specific procedures are initiated.

### Data collection

Data collection will be conducted over the first 18 months of the study and will consist of two complementary components: (1) collection of sociodemographic and clinical data and (2) assessment of skin barrier function using non-invasive biosensor-based measurements. This approach is intended to provide a comprehensive evaluation of both physiological and clinical determinants of skin barrier integrity in critically ill patients.

### Baseline data and clinical assessments

Sociodemographic and clinical data will be collected using a structured data collection form developed by the research team. The form consists of 41 items and includes information regarding age, sex, primary medical diagnosis, reason for ICU admission, severity of illness, dependency status, history of skin and tissue damage, pharmacological treatments, respiratory and nutritional support, laboratory findings relevant to skin barrier function, selected arterial blood gas parameters and nursing care practices related to skin integrity (table 1).

**Table 1 T1:** Outcome measures and assessment schedule

Outcome measure	Baseline (0–4 hours)	24 hours	48 hours	72 hours	96 hours	Day 14	Weekly until ICU discharge
Demographic characteristics	X	–	–	–	–	–	–
Clinical characteristics	X	X	X	X	X	X	X
APACHE II Score	X	–	–	–	–	–	–
Glasgow Coma Scale	X	X	X	X	X	X	X
Jackson/Cubbin Scale	X	X	X	X	X	X	X
mNutric Scale	X	–	–	–	–	–	–
Laboratory parameters	X	X	X	X	X	X	X
Nursing care variables	X	X	X	X	X	X	X
Transepidermal water loss (TEWL)	X	X	X	X	X	X	X
Stratum corneum hydration (SCH)	X	X	X	X	X	X	X
Skin pH	X	X	X	X	X	X	X
Local skin temperature	X	X	X	X	X	X	X
Pressure injury development	–	X	X	X	X	X	X
Pressure injury stage	–	X	X	X	X	X	X
Bates-Jensen wound assessment tool*	–	X	X	X	X	X	X
ICU length of stay	–	–	–	–	–	–	X†
ICU mortality	–	–	–	–	–	–	X†

* Assessed only in patients who develop pressure injuries.

† Recorded at ICU discharge or death.

APACHE II, Acute Physiology and Chronic Health Evaluation II; ICU, intensive care unit; mNutric, Modified Nutrition Risk in Critically Ill.

Baseline data will be collected within the first 4 hours following ICU admission. Relevant clinical variables will subsequently be recorded prospectively throughout the ICU stay to capture time-dependent changes and potential influencing factors.

Severity of illness will be assessed using the Acute Physiology and Chronic Health Evaluation II score, a validated instrument widely used to estimate disease severity and mortality risk among critically ill adults.^21^ Level of consciousness will be evaluated using the Glasgow Coma Scale and nutritional risk will be assessed using the Modified Nutrition Risk in Critically Ill score.^22
23^

PI risk will be assessed using the Jackson/Cubbin Pressure Area Risk Assessment Scale, which was specifically developed for intensive care populations and consists of 12 items evaluating age, tissue viability, skin condition, medical history, mobility, mental status, haemodynamic status, oxygen requirements, respiratory status, nutritional status, hygiene and continence. A total score of 29 or below is considered indicative of high PI risk.^24^

PIs will be classified according to the National PI Advisory Panel (NPIAP), European Pressure Ulcer Advisory Panel (EPUAP) and Pan Pacific PI Alliance (PPPIA) classification system.^1^

For participants who develop PIs, wound severity and healing progression will be evaluated using the Bates-Jensen Wound Assessment Tool (BWAT). The BWAT is a validated multidimensional instrument consisting of 13 wound characteristics that provide a standardised assessment of wound status over time.^25^

### Assessment of skin barrier function

Skin barrier function will be evaluated using a standardised measurement protocol and a dedicated Skin Integrity Monitoring Form developed by the research team. This form will be used to systematically record repeated measurements of TEWL, SCH, skin pH and local skin temperature across predefined anatomical regions.

### Measurement devices

Skin barrier function parameters will be assessed using non-invasive biophysical measurement devices. All devices are certified, used in clinical and academic research, and do not compromise skin integrity or patient comfort (table 2).

**Table 2 T2:** Standardised measurement procedures for skin barrier function assessments

Parameter	Device	Anatomical sites	Measurement procedure	Unit
Transepidermal water loss (TEWL)	Vapometer (Delfin Technologies)	Sacrum, right and left trochanters, right and left scapular regions, right and left lateral lower extremities, posterior neck, corresponding control sites and PI-affected skin	Probe positioned perpendicular to the skin surface according to manufacturer recommendations	g/m²/h
Stratum corneum hydration (SCH)	MoistureMeterSC (Delfin Technologies)	Same sites as above	Probe applied using standardised contact pressure according to manufacturer recommendations	Arbitrary Units (AU)
Skin pH	PH5F pocket pH Meter (Apera Instruments)	Same sites as above	Flat electrode gently applied to the skin until a stable reading is achieved	pH units
Local skin temperature	Integrated temperature sensor of the Vapometer	Same sites as above	Recorded simultaneously during TEWL assessment	°C

Standardisation procedures.

✓ Measurements performed by trained researchers using a standardised protocol.

✓ Devices calibrated according to manufacturer recommendations before data collection sessions.

✓ Non-invasive assessment procedures used for all measurements.

✓ Identical measurement procedures applied across all anatomical sites and time points.

✓ Assessments performed within the first 4 hours of ICU admission, at 24, 48, 72 and 96 hours, on day 14, and weekly thereafter until ICU discharge.

✓ Corresponding control sites assessed alongside all PI-prone and affected anatomical sites.

✓ TEWL values calculated as the mean of two consecutive measurements.

✓ Measurements recorded immediately in the study database following assessment.

✓ Device probes cleaned and disinfected between patients using hospital-approved disinfectants in accordance with institutional infection prevention policies and manufacturer recommendations.

✓ Pressure injury sites assessed using the same standardised procedures, with measurements obtained from peri-wound skin when direct measurement of the wound bed is not appropriate.

PI, Pressure Injury.

### Transepidermal water loss and skin temperature

TEWL and local skin temperature will be measured using the Vapometer,^26^ a portable closed-chamber evaporimeter widely used for skin barrier function assessment. The device provides objective, non-invasive measurements of water vapour evaporation from the skin surface. To improve measurement reliability, two consecutive measurements will be obtained from each anatomical site, and the mean value will be used for analysis.^19
27^ The device will be calibrated according to the manufacturer’s recommendations before each measurement session.

### Stratum corneum hydration

SCH will be assessed using the MoistureMeterSC.^28^ This device uses dielectric measurement technology to quantify tissue water content and provide objective information regarding skin hydration status.^14
29^ The device has been widely used in skin integrity research and enables rapid, non-invasive assessment of tissue hydration.^30
31^

### Skin surface pH

Skin surface pH will be measured using the PH5F pH Meter.^32^ This portable, non-invasive device measures skin surface acidity through direct contact with the skin. Measurements will be continued until the reading stabilises, and calibration procedures will be performed according to the manufacturer’s instructions before each data collection session.

### Outcomes

#### Primary outcomes

The primary outcomes of the study are skin barrier function parameters measured at predefined anatomical sites, including TEWL, SCH, skin surface pH and local skin temperature. These parameters will be assessed repeatedly throughout the ICU stay to evaluate temporal changes in skin barrier function and to investigate their relationship with PI development.

#### Secondary outcomes

Secondary outcomes include PI incidence, time to PI development and PI severity according to the NPIAP, EPUAP and PPPIA classification system. Among patients who develop PIs, wound progression and healing status will be evaluated using the Bates-Jensen Wound Assessment Tool. Additional secondary outcomes include ICU length of stay and ICU mortality.

#### Exploratory outcomes

Exploratory analyses will investigate differences in skin barrier function parameters between patients who develop PIs and those who do not, associations among the measured biophysical parameters, longitudinal trajectories of skin barrier function across different anatomical sites and clinical and physiological determinants associated with alterations in skin barrier function.

#### Data collection methods

Biophysical measurements will be obtained from anatomical regions commonly identified as PI-prone sites in critically ill patients, including the sacrum, bilateral trochanters, bilateral lateral lower extremities, bilateral scapular regions and the posterior neck.

A repeated-measures approach will be used to evaluate both short-term and longitudinal changes in skin barrier function. This approach was selected based on previous studies in which repeated biophysical assessments were successfully applied to monitor temporal changes in skin integrity over time.^18
33–35^ The initial assessment will be performed within the first 4 hours of ICU admission. Subsequent measurements will be conducted at 24, 48, 72 and 96 hours, on day 14, and weekly thereafter until ICU discharge (table 2).

For each anatomical measurement site, a corresponding control area located approximately 10 cm away will also be assessed. To ensure consistency across repeated measurements, predefined circular measurement areas will be marked and used throughout follow-up.

All measurements will be conducted by trained researchers according to a standardised protocol. During each measurement session, one researcher will perform the measurements, a second researcher will verify the readings and a third researcher will record the data electronically. Paper-based forms will be available as a backup in case of technical issues.

If a PI develops, measurement procedures will be adapted according to injury stage. For Stage I PIs, measurements will be obtained directly from the affected site. For Stage II or more advanced PIs, measurements will be performed on the nearest adjacent area of intact skin. In both situations, the corresponding control site will also be assessed. Wound progression will be monitored using the Bates-Jensen Wound Assessment Tool.

To minimise the influence of mechanical loading, measurements will be performed following routine patient repositioning and approximately 15–20 min after pressure removal. All anatomical regions, except the sacrum, will be assessed bilaterally.

The duration of each measurement is approximately 15–20 s for most devices, whereas pH measurements require approximately 30 s for stabilisation. If haemodynamic instability occurs during the procedure, measurements will be immediately discontinued to ensure patient safety.

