### Participants and sampling

All patients admitted to the ICU during the study period who meet the eligibility criteria will be invited to participate. Eligible patients who provide informed consent, either directly or via a legal representative, will be consecutively enrolled and followed longitudinally throughout their ICU stay.

The sample size was calculated using G*Power software based on previously reported differences in sacral stratum corneum hydration between patients who developed PIs and those who did not. In the reference study, sacral stratum corneum hydration was 17.7±3.78 AU in patients who developed pressure injuries and 20.0±3.92 AU in those who did not, corresponding to an effect size of approximately Cohen’s d=0.59.^20^ Assuming a two-sided significance level of 0.05, 90% statistical power and an allocation ratio of 1:2 based on the expected distribution of patients with and without pressure injury in the study setting, the minimum required sample size was calculated as 138 participants (46 with PI and 92 without PI). To account for an anticipated attrition rate of approximately 20%, the target sample size was increased to 165 participants.

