#### Statistical analysis

Statistical analyses will be performed using IBM SPSS Statistics V.29.0 and, where required for time-to-event analyses, R statistical software.

Descriptive statistics will be used to summarise demographic, clinical and skin barrier function characteristics. Prior to inferential analyses, data will be examined for completeness, outliers and distributional assumptions. Continuous variables will be assessed for normality using visual inspection methods (histograms and Q–Q plots) and the Shapiro-Wilk test. Descriptive statistics will be reported as mean and SD or median and IQR, as appropriate. Continuous variables will be reported as mean and SD or median and IQR, as appropriate, whereas categorical variables will be presented as frequencies and percentages.

Changes in TEWL, SCH, skin pH and local skin temperature over time will be examined using repeated-measures analyses. To account for repeated observations within individuals and varying follow-up durations, linear mixed-effects models will be used as the primary analytical approach.

Comparisons between patients who develop PIs and those who do not will be performed using appropriate parametric or non-parametric methods according to data distribution. For patients who develop PIs, measurements obtained from affected sites will be compared with corresponding control sites using paired analyses.

The association between longitudinal skin barrier function parameters and incident PI development will be evaluated using discrete-time survival analysis. Follow-up will be divided according to the predefined skin assessment intervals, thereby accounting for the interval-censored nature of PI onset. TEWL, SCH, skin pH and local skin temperature will be incorporated as time-varying covariates using the most recent measurement available for each assessment interval. Death and ICU discharge before PI development will be considered competing events and will be explicitly accounted for in the time-to-event analyses. Potential determinants, including demographic characteristics, illness severity, PI risk scores, laboratory findings, treatments and nursing care practices, will first be examined in univariable analyses. Multivariable models will subsequently be constructed using a limited number of prespecified clinically relevant covariates, according to the number of observed PI events, to minimise model overfitting.

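### Pressure injury status is scheduled only at the device visits, with no check from 96 hours to day 14 or at ICU exit, so an injury that starts after a patient's last visit can go unrecorded

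*Protocol article*

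**What the plan says.** - **Visit times** (Data collection methods): "Subsequent measurements will be conducted at 24, 48, 72 and 96 hours, on day 14, and weekly thereafter until ICU discharge".
- **What is assessed when** (Table 1, "Outcome measures and assessment schedule"): the rows for PI development and PI stage are ticked at 24, 48, 72 and 96 hours, day 14 and weekly, exactly as the device readings are after baseline. No column lies between 96 hours and day 14.
- **What is taken at exit** (Table 1 footnote): "Recorded at ICU discharge or death". The mark is on ICU length of stay and ICU mortality only.
- **Analysis intervals** (Statistical analysis): "Follow-up will be divided according to the predefined skin assessment intervals, thereby accounting for the interval-censored nature of PI onset".
- **Leaving the ICU** (Statistical analysis): "Death and ICU discharge before PI development will be considered competing events and will be explicitly accounted for in the time-to-event analyses".
- **Outcomes affected** (Secondary outcomes): "Secondary outcomes include PI incidence, time to PI development and PI severity".
- **Follow-up** (Participants and sampling): patients are "consecutively enrolled and followed longitudinally throughout their ICU stay", so nothing after ICU exit can fill the gap.

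**The concern.** Interval censoring handles an event known to lie between two checks. It needs the second check. A patient who leaves the ICU before the next visit has none, so an injury that began after the last visit has no scheduled route into the data. The gap from 96 hours to day 14 is where this matters most, because it is long and many ICU patients may leave during it.

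Two consequences follow. Recorded PI incidence is too low. True cases also enter the analysis as competing events and as members of the no-PI group, which pulls PI versus no-PI contrasts towards zero. Those contrasts are the basis of the sample size, and the article lets the number of observed PI events limit the size of the multivariable models. For patients who do stay, onset within the gap is known only to within 10 days and is recorded late.

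**Working it through.** **1. Length of the gap.** 96 hours is day 4, and 14 − 4 = 10 days.

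**2. One patient traced through the plan.** PI starts on day 6 and the patient is discharged on day 10. The last PI check was on day 4 (no PI) and the next would be on day 14 (patient gone). Exit items are length of stay and mortality. No PI is on record, so under the Statistical analysis section the patient is a discharge before PI.

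**3. The plan's own figure.** Participants and sampling: "Assuming a two-sided significance level of 0.05, 90% statistical power and an allocation ratio of 1:2", with d = 0.59. Smaller group = (1 + 1/2)(1.960 + 1.282)²/0.59² = 45.3, so 46. The total is 46 + 92 = 138, as stated; noncentral-t power is 0.900.

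**4. Size of the loss.** The article gives no length of stay or PI rate, so these are assumptions: exponential stay with mean M days (m = 1/M), constant PI hazard h per day, λ = m + h, and detection only at visits on days 1, 2, 3, 4, 14, 21 and so on.

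- True incidence: I = h/λ
- Leave before day 14, given present at 96 hours: 1 − exp(−10m)
- PIs starting between visits a and b: I[exp(−λa) − exp(−λb)]
- Of these, recorded: [exp(−ha) − exp(−hb)]·exp(−mb)
- Missed: the difference

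Example with M = 10, h = 0.05, chosen because I = 0.05/0.15 = 33% matches the planned 1:2 split. For the gap (a = 4, b = 14):

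- starting: 0.3333 × (0.5488 − 0.1225) = 0.1421
- recorded: (0.8187 − 0.4966) × 0.2466 = 0.0794
- missed: 0.0627, and 0.0627/0.3333 = 19% of all PIs

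Recorded incidence is 33.3% − 6.3% = 27% counting gap misses only. Summing the missed term over all intervals gives 25% of PIs missed and 25% recorded incidence.

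| Mean stay (d) | Hazard/d | True incidence | Leave day 4–14 | PIs missed, gap | PIs missed, all intervals | Mean onset, true (d) | Mean onset, recorded (d) |
|---|---|---|---|---|---|---|---|
| 5 | 0.03 | 13% | 86% | 25% | 33% | 4.3 | 4.7 |
| 5 | 0.05 | 20% | 86% | 24% | 32% | 4.0 | 4.3 |
| 7 | 0.03 | 17% | 76% | 23% | 31% | 5.8 | 6.9 |
| 7 | 0.05 | 26% | 76% | 23% | 29% | 5.2 | 6.2 |
| 10 | 0.03 | 23% | 63% | 19% | 26% | 7.7 | 9.7 |
| 10 | 0.05 | 33% | 63% | 19% | 25% | 6.7 | 8.5 |
| 14 | 0.03 | 30% | 51% | 14% | 21% | 9.9 | 12.5 |
| 14 | 0.05 | 41% | 51% | 14% | 20% | 8.2 | 10.7 |

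A second set of assumptions holds true incidence at one third and sets median stay to 4, 7, 10 or 14 days. PIs missed because of the gap are then 22, 19, 14 and 9% of all PIs; over all intervals, 29, 25, 20 and 16%.

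**5. Power at d = 0.59 with 25% recorded incidence (noncentral t).**

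- 138 analysed, 34/104: 0.843
- 165 analysed, 41/124: 0.902

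These leave the effect size intact. If missed cases resemble recorded ones, the no-PI mean shifts. At 138, 46 − 34 = 12 of the 104 controls are true cases, d = 0.59 × 92/104 = 0.52, and power is about 75%. At 165, 55 − 41 = 14 of 124 are true cases, d = 0.59 × 110/124 = 0.52, and power is about 82%.

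**The case against.** **PIs seen between visits may be captured anyway.** The baseline section says relevant clinical variables are recorded through the ICU stay, and the measurement section adapts procedures once a PI develops without limiting this to a visit. The article is condensed, and the full protocol and case report forms are not shown. This stands in part: nowhere does the article say that a missed PI is coded as a competing event. That is an inference from Table 1 and the Statistical analysis section read together. But Table 1 gives PI development its own row tied to the visits, and no route for capture between visits is described.

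**Weekly until discharge might include an exit check.** It does not say so. It marks when the weekly series, which starts after day 14, ends. Table 1 has a separate mark for exit items, and the PI rows lack it.

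**The primary outcomes are untouched.** Largely true. They are the barrier parameters over time, analysed by mixed models that allow unequal follow-up. PI incidence and time to PI are secondary, and the PI versus no-PI contrast is exploratory, although the sample size rests on it.

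**Stronger readings that the documents do not support.** A reader might infer that:

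- the gap alone loses up to a third of PIs; the 20–33% includes misses in the daily and weekly intervals, and the gap accounts for 14–25%;
- power falls to 84%; that holds only if 138 patients are analysed, whereas the target is 165;
- time to PI is biased downwards; in all eight scenarios the mean recorded time is later than the true mean, because a PI starting in the gap in a patient who stays is first seen on day 14.

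**Conclusion.** The point holds. As written, Table 1 and the analysis intervals leave an injury that starts after the last visit before exit with no scheduled check to record it, and neither interval censoring nor competing-event handling repairs that. The downward direction for PI incidence is secure, and dilution of the PI contrasts follows if missed cases resemble recorded ones.

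The size is conditional, since stay and hazard are assumed throughout. With mean stay 5–14 days and hazard 3–5% per day, 14–25% of PIs are missed because of the gap and 20–33% over all intervals. In the example with 33% true incidence, 27% is recorded counting gap misses only and 25% counting all. The loss of cases alone leaves power near 90% if all 165 are analysed; misclassified controls would lower it further. In patients who stay, onset in the gap is recorded late and is uncertain by up to 10 days.

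**What to change.** Recruitment had not started when the article was submitted, so the change can be made before any data are lost.

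1. In Table 1, add PI status and stage to the items recorded at ICU discharge or death.
2. Between device visits, record PI presence, site, stage and first-seen date from the ward's routine nursing skin inspections, and flag the source of each PI date (research assessment or routine chart).
3. In the Statistical analysis section, define the PI event intervals from these dates rather than from the device visits alone. The choice of link function can stay with the analysis plan.
4. Leave the device visits unchanged.

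If the full protocol already captures PIs between visits, state this in Table 1 and the Statistical analysis section; the exit item is still needed. In the second set of assumptions, a daily check without an exit check would still miss about 8.5% of PIs at a median stay of 4 days and 2.5% at 14 days.

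The cost is one chart item on the days between visits and one exit check, with no extra device sessions. The downside is that routine inspection is less standardised than the research assessment, which is why the source flag matters. The change does not shorten the age of the barrier readings: a 96-hour value may still be carried for up to 10 days as the most recent measurement, and the report should say so.

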## Introduction

 Pressure injuries (PIs) are localised tissue damages that typically develop over bony prominences as a result of prolonged pressure or the combined effect of pressure and shear forces on the skin and/or underlying soft tissue.^1
^Patients monitored in intensive care unit (ICU) constitute a particularly high-risk group for PIs due to factors such as immobility, hypoperfusion, vasopressor use, inadequate nutrition, mechanical ventilation, invasive devices, fluid and electrolyte imbalances and haemodynamic instability, all of which reduce tissue tolerance and accelerate PI development.^2^

The prevalence and incidence of PIs acquired in intensive care settings remain substantial worldwide. In the DecubICUs study, PIs were identified in 6747 of 13 254 patients followed in 1117 ICUs, with 59.2% of these lesions developing during ICU stay.^3^ In addition to their clinical consequences, PIs impose a considerable economic burden on healthcare systems.^4–7^

The prevention and early detection of PIs are recognised as key indicators of nursing care quality. Current clinical guidelines recommend evidence-based interventions including risk assessment, comprehensive skin evaluation, protective skin care, regular repositioning, early mobilisation, nutritional support and the use of pressure-redistributing support surfaces.^1
8^ Among these strategies, skin assessment plays a central role in identifying early tissue damage and guiding preventive interventions.^9^ However, visual skin assessment remains dependent on clinician judgement and may be subject to variability, potentially limiting the objectivity and sensitivity of findings.^10^

Consequently, increasing attention has been directed toward objective approaches for assessing skin barrier function. Biophysical measurements obtained through biosensory technologies suggest that PI pathophysiology, including ischaemia, reperfusion injury, cellular death, inflammation and impaired lymphatic drainage, may be reflected by alterations in skin barrier integrity before visible clinical signs emerge.^11
12^ Parameters commonly associated with skin barrier function include transepidermal water loss (TEWL), skin pH, subepidermal moisture, stratum corneum hydration (SCH), erythema, skin temperature, sebum and transcutaneous oxygen levels.^13–16^

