Inter-rater agreement for PI risk assessments and PI classification will be evaluated using Cohen’s kappa coefficient. In addition to statistical significance, effect sizes will be reported to facilitate interpretation of the clinical relevance of findings. Statistical significance will be set at p<0.05.

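### Pressure injury status and stage are judged by eye at the device-reading time points, and nothing stated keeps the raters from knowing the readings

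*Protocol article*

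**What the plan says.** All references are to the protocol article.

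- **Schedule.** In Table 1 (Baseline data and clinical assessments) the row "Pressure injury development", the PI stage row and the row for the Bates-Jensen tool (BWAT, only in patients with a PI) are marked at 24, 48, 72 and 96 hours, day 14 and weekly. TEWL, hydration (SCH), pH and temperature carry the same marks plus baseline. Data collection methods agrees: "Subsequent measurements will be conducted at 24, 48, 72 and 96 hours, on day 14, and weekly thereafter until ICU discharge".
- **Roles.** In each measurement session "one researcher will perform the measurements, a second researcher will verify the readings and a third researcher will record the data electronically". All three tasks concern the device values.
- **PI rating.** "PIs will be classified according to the National PI Advisory Panel (NPIAP), European Pressure Ulcer Advisory Panel (EPUAP) and Pan Pacific PI Alliance (PPPIA) classification" system. No rater is named.
- **Link between rating and probing.** "If a PI develops, measurement procedures will be adapted according to injury stage": Stage I is probed on the lesion, higher stages on adjacent intact skin.
- **Nature of the judgement.** The Introduction says that "visual skin assessment remains dependent on clinician judgement and may be subject to variability, potentially limiting the objectivity and sensitivity of findings".
- **Check on the rating.** "Inter-rater agreement for PI risk assessments and PI classification will be evaluated using Cohen’s kappa coefficient".
- **Use of the rating.** "The association between longitudinal skin barrier function parameters and incident PI development will be evaluated using discrete-time survival analysis". The same section compares patients who develop a PI with those who do not.

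**The concern.** A study of whether a marker goes with an outcome needs the outcome judged without knowledge of the marker. Here the outcome rests on visual judgement, the marker is read at the same time points, and the plan states no masking and no locked order of entry.

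The team also has a direction in mind. The Discussion reports higher TEWL, higher pH and lower moisture in patients with PIs. A rater who knows that a site has read abnormally may be readier to call an equivocal finding a PI. That produces misclassification related to the reading, which moves the association in the expected direction. If the true association is nil or already in that direction, this is away from the null.

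At stake are the PI versus no-PI comparison, on which the sample size is based, the survival analysis of incident PI, and the secondary outcomes of PI incidence, time to PI and severity. An unmasked call cannot be made again blind from the data the article describes.

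**Working it through.** **1. Which routes are open?**

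| Route from reading to PI call | What the article says | Status |
|---|---|---|
| The reading at this visit informs the first call at this visit | Probe placement depends on stage, so the skin must be inspected before probing | Largely closed by implication |
| Earlier readings inform this visit's call | The same marked areas are re-measured; values go into the study database at once (Table 2); Data management limits access to authorised team members, with no restriction by role | Open |
| The call is revised after the reading | No lock or time stamp on the PI entry is stated | Open |

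The second route matters for the model. Statistical analysis uses the latest available reading in each interval as a time-varying covariate, so an earlier value that a rater could know may also be the predictor.

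**2. Which calls are exposed?** An event and its time are set by the call between no PI and PI. Where the first stage called is Stage I, that boundary is the finest and the most open to expectation. This is reasoning; the documents give no misclassification rates by stage. ICU stay and mortality are not exposed.

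**3. Does kappa detect it?** No. Kappa measures agreement between raters. Two raters who know the same values can agree and share the same bias.

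**4. Which analyses are exposed?** The PI versus no-PI comparison and the survival model use the PI call directly. The mixed models of change over time do not use it as outcome. A PI call reaches them only through the probe-site rule for Stage II and above.

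**5. Illustration A, odds ratio.** The point rests on no stated figure. The PI share comes from Participants and sampling: 46 with and 92 without PI, 46/138 = 33.3%. That sample size reproduces: noncentral t, d = 0.59, two-sided 0.05, ratio 1:2 gives 46 + 92 with power 0.9005. Assume no true association, and x extra PI calls per 100 patients with a high reading. Odds = p/(1 − p); odds ratio = odds(33.3% + x)/odds(33.3%), where odds(33.3%) = 0.500.

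| x (assumed) | PI share, high readings | Odds | Odds ratio |
|---|---|---|---|
| 2 | 35.3% | 0.546 | 1.09 |
| 5 | 38.3% | 0.621 | 1.24 |
| 10 | 43.3% | 0.764 | 1.53 |

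**6. Illustration B, false-positive rate.** Simulation with N = 138, about one third with PI, a standard normal reading unrelated to true PI, and 4000 runs per setting. A share of patients is equivocal; for them the log odds of a PI call are log(0.5) + log(OR) × reading. Test: two-sample t-test, two-sided 5%.

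| Equivocal (assumed) | OR per SD 1.5 | 2 | 3 |
|---|---|---|---|
| 10% | 5.4% | 6.7% | 7.5% |
| 20% | 6.4% | 10.6% | 16.6% |
| 30% | 9.7% | 18.8% | 32.3% |

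The simulation error at 5% is √(0.05 × 0.95/4000) = 0.34 percentage points, so 5.4% cannot be told from nominal. The mean spurious difference runs from 0.04 to 0.27 SD, against the planned 0.59.

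Both illustrations work at patient level. Neither is the planned interval-level model, and every rate of influence in them is an assumption.

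**The case against.** The strongest reply is that the point rests on a silence. The three session roles concern device readings; the article does not say that these people rate PIs. Agreement between raters is planned, so at least two raters exist, unidentified. A standardised protocol and a monitoring form are mentioned but not shown, and they may fix order and masking.

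Secondly, the probe rule already puts inspection first at each visit. Memory of earlier values is a weak route: eight sites and eight control sites with four parameters make 16 × 4 = 64 values per session, no cut-off for an abnormal reading is given, and after 96 hours the gaps are about ten days and then a week.

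Thirdly, the primary outcomes are the device parameters, the mixed models are the primary approach, and the article claims association only.

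Much of this stands. A reader might infer that the measuring team rates the PIs and that the bias is therefore present; the documents do not say so. A reader might infer that the reading at a visit drives the call at that visit; the probe rule speaks against it.

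What does not stand is that nothing is left. The article sets out session roles, stage-dependent probing and the agreement check in some detail, and as described they leave earlier values open to the rater and the rating open to revision. Nor are the PI analyses marginal: the sample size is built on the PI contrast, and the Primary outcomes section includes the relation to PI development.

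**Conclusion.** The concern holds in limited form. PI presence and stage depend on visual judgement, fall at the same time points as the readings, and have no stated protection from knowledge of current or earlier values beyond the implied order of inspection at a visit. The PI versus no-PI comparison and the discrete-time survival analysis could be biased away from the null, mainly through borderline Stage I calls.

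The size cannot be estimated from the documents. The odds ratios of 1.09 to 1.53 and the false-positive rates of 5.4% to 32.3% show what assumed degrees of influence would do. They should not be read as expected bias, and with 10% equivocal findings the error rate stays near nominal.

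A reader might also infer that the primary analysis is compromised. It is not: the mixed models of change over time depend on PI calls hardly at all. That PI and device assessments share a session, and not only a time point, is itself an inference, though the probe rule supports it.

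The change is worth making because it is nearly free, and recruitment had not begun when the article was submitted.

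**What to change.** At each visit, enter PI status, stage and (where it applies) BWAT in a time-stamped field that locks before the first probe is applied. Use a form or screen that shows no current or earlier device values. Apply this to every rater who contributes to the kappa analysis, so that agreement is measured between raters working under the same restriction.

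Keep the separate measure, verify and record roles for the readings, since they protect the primary outcomes. Where the existing team allows, the PI rating should come from a member who did not handle that patient's earlier readings.

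The cost is a fixed order of data entry, a change to the form or database, and some scheduling of roles. Memory of earlier values is not fully removed where a rater has handled that patient before; the report should say so.
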